### Primary endpoint

The primary endpoint of this study is an evaluation of the safety and tolerability of metformin therapy in overweight and obese young adults and children with dengue. The number of clinical and laboratory adverse events (AEs) occurring during the five study days (
Table 1), will be compared between the treatment population and the non-treated controls.

**Table 1. T1:** Adverse events.

1- Worsening level of consciousness (fall in GCS ≥ 2 points)
2- Change in blood pressure (PP < 20 mmHg, SBP < 90 mmHg or unmeasurable BP)
3- Vomiting (≥ 3 episodes separated by 15 minutes/ 24 hours)
4- Epigastric abdominal pain
5- Diarrhoea (≥ 5 episodes/24 hours)
6- Mucosal bleeding
7- Rash, urticaria
8- Increased lactate (≥ 3 mmol/L)
9- Episode of hypoglycaemia (glucose < 3.9 mmol/L or < 70 mg/dL)
10- Increased liver enzyme (AST or ALT > 400 U/L)
11- Acute kidney injury (eGFR reduction of >50% or < 30 ml/mn/1,73m ^2^ or plasma creatinine >2 fold increase from baseline)
12- Thrombocytopenia (Platelet < 20.000/uL)
13- Other event, specify: [________________________________________]

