### Aims of the trial

We hypothesize that metformin therapy given early in the course of disease will attenuate obesity-induced lipid-inflammatory mediators and improve clinical parameters in dengue patients with obesity. In addition, the therapy could reduce viral replication through AMPK activation and immunomodulation in such patients.

This study aims to formally assess metformin as adjunctive therapy for dengue in overweight and obese patients.

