### Statistical considerations

***Sample size.*** This is an exploratory study focusing primarily on safety, and there are no preliminary data regarding the effects of metformin in dengue on which to base a sample size calculation. A target sample size of 60 patients was chosen based on clinical judgement and feasibility considerations. Using the trend in VCAM over time, which is one of the secondary endpoints, by assuming a slope of change in concentration over time at 0.34 (log
_2_VCAM concentration per day, data based on biomarkers of endothelial function in dengue), we conducted a power calculation using a t-test to compare effects on endothelial function between two groups. It is suggested this study will have a power of 80% to detect a difference of at least 0.023 (log
_2_VCAM concentration per day) in the slope of change.

***Statistical analysis.*** The primary analysis population will include all patients from cohort 1 and cohort 2, plus 60 controls as mentioned previously. Baseline characteristics and outcomes will be summarised for each treatment group. The cohort of patients enrolled in this study will form the active treatment group, while the control group will consist of overweight and obese dengue patients that participated in a matched cohort observational study, none of whom received metformin therapy. Continuous variables will be described using medians and quartiles, while categorical variables will be described in terms of frequencies and percentages.

The primary endpoint (number of AEs), will be compared between the treatment groups using negative binomial regression model. The clinical, biomarker, immunological will be compared between the treatment arms using linear regression or random effects model for continuous endpoints, and Cox regression for time-to-event endpoints (fever clearance time, time to first undetectable viremia measurement, time to first negative NS1 measurement). All comparisons will be adjusted for age, sex, and day of illness, as patients will not be randomized. For percentage increase in HCT and area under the curve of viraemia, comparisons will be also adjusted for the pre-dose value of the respective marker.

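### The primary safety count adds drug-type and dengue-course events together, so a total rate ratio near or below 1 can hide or dilute a rise in drug-type events

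*Protocol article*

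**What the plan says.** The Primary endpoint section states the purpose: "The primary endpoint of this study is an evaluation of the safety and tolerability of metformin therapy in overweight and obese young adults and children". The measure is "The number of clinical and laboratory adverse events (AEs) occurring during the five study days", as listed in Table 1, compared between treated patients and untreated controls. Statistical considerations fixes the analysis: "The primary endpoint (number of AEs), will be compared between the treatment groups using negative binomial regression model", adjusted for age, sex and day of illness.

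Table 1 has thirteen items and no weights. They fall into three sets:

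- **Six are kinds of event also named in the stopping list under Safety reviews:** vomiting, diarrhoea, lactate, hypoglycaemia, liver enzymes and kidney function. Examples are "Increased lactate (≥ 3 mmol/L"), "Episode of hypoglycaemia (glucose < 3.9 mmol/L or < 70 mg/dL") and "Diarrhoea (≥ 5 episodes/24 hours").
- **Four describe the course of dengue:** falling consciousness, low blood or pulse pressure, mucosal bleeding, and platelets ("12- Thrombocytopenia (Platelet < 20.000/uL")).
- **Three are unassigned:** epigastric pain, rash, and an open category for other events.

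Aims of the trial hypothesises that early metformin will "improve clinical parameters in dengue patients with obesity". Secondary endpoints include the platelet nadir and the highest AST/ALT. Severity grade and likely relation to treatment are both recorded, but neither enters the primary count.

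**The concern.** The question is whether metformin is safe and tolerable, but the number meant to answer it can move for two unrelated reasons. More gastrointestinal, lactate or glucose events push it up. Milder dengue pushes it down. If the trial's hypothesis is right, efficacy lowers the safety count. If it is wrong, the dengue events still dilute any change in the drug-type events.

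The protocol already draws this distinction elsewhere: for serious-event reporting it sets apart events that only reflect progression to severe dengue. The primary comparison does not.

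The Discussion makes a larger randomised trial depend on safety being established, and this count is the only primary evidence for that. A ratio at or below 1 could be read as good tolerability while drug-type events have risen.

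A smaller point adds to this. Nothing in Table 1 limits the count to new or worsened events. The exclusion criteria do not cover non-severe mucosal bleeding, rash or epigastric pain. A patient with exactly three vomiting episodes in 24 hours is not excluded, yet already meets Table 1's number of episodes.

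**Working it through.** **The plan's own figure.** There is none for this endpoint. The only power statement (80% for a VCAM slope difference of 0.023) concerns a secondary endpoint and gives no standard deviation, so it has no bearing here.

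**Inputs.** From the protocol: 60 treated and 60 control patients, negative binomial model. Assumed, because the protocol gives no values: event rates per patient, dispersion k of 0, 0.5 or 1, and two-sided 5% significance. Covariate adjustment is ignored.

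**Formulas.** With mean counts m0 (control) and m1 (metformin):

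- RR = m1/m0
- SE(log RR) = √{[(1/m0 + k) + (1/m1 + k)]/60}
- Power = Φ(|log RR|/SE − 1.96) + Φ(−|log RR|/SE − 1.96)

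**Drug-type events alone, doubling from 0.3 to 0.6.** At k = 0.5, SE = √[(3.333 + 0.5 + 1.667 + 0.5)/60] = √0.100 = 0.316. Then 0.693/0.316 = 2.19, and power is 59%. At k = 0 and k = 1 it is 67% and 53%.

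**The same doubling inside the pooled count:**

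| Dengue-course events, control → metformin | Total, control → metformin | Pooled RR | Chance the pooled test rejects (k = 0 / 0.5 / 1) |
|---|---|---|---|
| 0.9 → 0.9 | 1.2 → 1.5 | 1.25 | 29% / 19% / 15% |
| 0.9 → 0.6 | 1.2 → 1.2 | 1.00 | 5% / 5% / 5% |
| 1.5 → 0.9 | 1.8 → 1.5 | 0.83 | 25% / 16% / 12% |

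The first row has no dengue benefit at all, and the signal is still diluted. In the last row, the pooled estimate points towards fewer events on metformin although drug-type events have doubled.

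**Other assumed rates.** With drug-type events still going from 0.3 to 0.6, dengue events unchanged at 1.5 give a pooled RR of 2.1/1.8 = 1.17, and a fall from 1.5 to 1.05 gives 1.65/1.8 = 0.92. Across three sets of rates that cancel exactly (0.3→0.6 with 0.9→0.6; 0.2→0.4 with 0.8→0.6; 0.3→0.75 with 1.5→1.05), power for the drug-type count alone runs from 41% to 91%, against 5% for the total.

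**Simulation check** (500 trials per scenario, k = 0.5, negative binomial fit). First row: pooled 22%, drug-type 63%. Second row: pooled 5%, drug-type 60%. Both agree with the formulas to within simulation error.

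**Precision of a null total.** With 1.2 events per patient in both groups and k = 0.5, SE = √[(0.833 + 0.5) × 2/60] = 0.211. A ratio of 1.00 then has a 95% interval of about 0.66 to 1.51.

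**Cost of splitting.** At k = 0.5 and equal means, SE is √[(1/0.6 + 0.5) × 2/60] = 0.269 for 0.6 events per patient and √[(1/1.5 + 0.5) × 2/60] = 0.197 for 1.5. The interval factors are exp(1.96 × 0.269) ≈ 1.7 and exp(1.96 × 0.197) ≈ 1.5.

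**The case against.** **No safety rule is stated.** A reader might infer that a non-significant total would lead to metformin being called safe. The protocol contains no such rule. The Discussion speaks only of safety being established and does not say how. This stands, so the point concerns what the total can show, not a declared decision.

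**The hypothesis is general.** It speaks of clinical parameters and does not name consciousness, blood pressure or bleeding. Among Table 1 items, only platelets and AST/ALT reappear as secondary endpoints. This stands: expected benefit on the other disease-course items is a reasonable reading but is not stated. Dilution needs no such benefit.

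**The split is not clean.** It is tempting to file every organ-level event as dengue progression. The documents do not support that for AST/ALT and kidney function, which the stopping list names. Nor is that list a perfect divider: its clause opens with any adverse event and then names examples, severe dengue is a separate reason to stop, and its vomiting thresholds differ from Table 1's. The allocation must therefore be declared in advance and tested.

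**An all-cause count against concurrent controls is defensible.** It avoids subjective attribution in an open-label study. This stands as a reason to keep the total, but a split by event type needs no attribution either.

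**Component information exists.** Descriptive summaries, grades, relatedness, daily review and the Data Monitoring Committee could all reveal a rise in lactate or gastrointestinal events, and an analysis plan may add component tables. It would be wrong to say that the trial could not see such a rise. None of this changes the stated primary comparison.

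**The rates are assumed, and exact cancellation is a chosen case.** This stands, and is why a range is shown. Much of the weakness also comes from 60 per group: at k = 0.5 the separate count still misses a doubling about 41% of the time.

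**Baseline symptoms** should be broadly similar in the two groups, which share entry criteria. Carry-over is thus mainly noise, and a minor part of the point.

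**Conclusion.** The point holds in a limited form. The stated primary comparison is one unweighted count that mixes drug-type and dengue-course events, so a total rate ratio near or below 1 is compatible with a material rise in drug-type events. Under the assumed rates, a doubling of those events appears as a pooled ratio anywhere from 1.25 to 0.83, and the pooled test detects it far less often than the drug-type count does (15–29% against 53–67% when dengue events do not change). The mechanism does not depend on the assumed rates; its size does.

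The documents do not support the stronger conclusion that the trial would declare metformin safe on a null total. This is an inexpensive improvement to an exploratory study, not a defect that invalidates it.

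**What to change.** Before analysis, assign every Table 1 item to one of two counts, using the kinds of event named in the Safety reviews stopping list:

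- **Drug-safety count:** vomiting, diarrhoea, lactate, hypoglycaemia, AST/ALT and renal events.
- **Disease-course count:** consciousness, blood pressure, mucosal bleeding and platelets.
- **Epigastric pain, rash and other events:** assigned to one of the two in advance, with the rule written down.

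Fit the same adjusted negative binomial model to each count. Count only events that are new or worsened since enrolment. Report each rate ratio with its 95% confidence interval beside the all-cause total, and base the safety conclusion on the drug-safety count rather than on the total alone. Because AST/ALT and renal events may reflect either drug or disease, repeat the analysis with them in the other group as a sensitivity analysis.

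This groups events for analysis only and changes no clinical threshold. The differing vomiting definitions in Table 1 and the stopping list should be reconciled by the sponsor.

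The cost is protocol or analysis-plan wording, with no new data. There are fewer events per count, so intervals widen: a 95% factor of about 1.7 instead of 1.5 under the assumed means of 0.6 and 1.5 events per patient.

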**Grade of the event**
Mild: Discomfort noticed but no disruption of normal daily activities
Moderate: Discomfort sufficient to reduce or affect daily activity
Severe: Inability to perform daily activity

### Secondary endpoints

The secondary endpoints are: fever clearance time (the time from enrolment to sustained body temperature <37.5°C for 48 hours); platelet nadir and highest AST/ALT between days 3 and 8 of illness; percentage increase in haematocrit (HCT) from baseline (using HCT obtained at the 28 day FU visit to reflect baseline); plasma viraemia (area under the log
_10_-transformed viraemia curve from study days 3 to 6); time from enrolment to first undetectable viraemia and first negative NS1 measurement; trend over time (5 days) in VCAM1, CRP, leptin, adiponectin, low density lipoprotein (LDL), and AMPK phosphorylation; and magnitude of activated/proliferating T and NK cells as well as frequency and phenotype of dengue-specific CD4+ and CD8+ T cells, quantified by flow cytometry at enrolment and hospital discharge.

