### Inclusion and exclusion criteria

Patients will be eligible for study enrolment if they: (i) are aged between 10 and 30 years; (ii) have a clinical diagnosis of dengue (based on World Health Organization (WHO) – Dengue guidelines)
^2^; (iii) are NS1 rapid antigen test positive; (iv) have BMI >25kg/m
^2^ (or BMI-for-age >1 SD); (v) are admitted within 72 hours of fever onset; (vi) agree to come back for FU visit between days 21–28 of illness; and (vii) provide written informed consent.

Exclusion criteria include: (i) pregnancy (confirmed by either clinical examination or urine dipstick for human chorionic gonadotrophin hormone); (ii) localising features suggestive of an alternative diagnosis; (iii) significant diarrhoea and/or vomiting (>3 episodes/24 hours); (iv) history of hypersensitivity to metformin; (v) current use of metformin or any other regular hypoglycaemic agent, including insulin; (vi) current use of any drug with significant metformin interaction (
*Extended data*
^46^); (vii) current treatment for heart failure or recent history of myocardial infarction (in the last year); (viii) presence of severe infection at enrolment, including severe dengue, central nervous system infection or septicaemia; (ix) baseline lactate level >2.0 mmol/L; (x) baseline blood glucose level <3.9 mmol/l (or <70 mg/dL); (xi) baseline liver impairment (alanine transaminase (ALT) and/or aspartate transaminase (AST) >250 U/L); and (xii) chronic renal impairment (glomerular filtration rate (GFR) <30 mL/min). Patients that are deemed unlikely to attend FU at 28 days from fever onset because of long travelling distance to the clinic will also be excluded.

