### Screening, enrolment and retention

Patients aged between 10 and 30 years that are admitted to one of the three study wards of the HTD, HCMC, Vietnam, with clinical suspicion of dengue and less than 72 hours of fever are invited to participate in the trial. After giving consent, patients are screened for their eligibility to commence treatment with the trial drug by the study physicians. Blood samples are collected to test for NS1, and AST, ALT and creatinine levels and in female patients, a urine sample is collected for a pregnancy test. Glucose and lactate levels are measured using point-of-care (POC) tests.

All patients will be asked to come back for a final FU visit at 28 days after the onset of fever. Patients will be contacted 3–5 days prior to the FU visit to arrange an appropriate appointment date and time. Any case who misses the FU visit will be contacted by phone either to reschedule the visit or to collect information if patients could not arrange their time to come back. If the patients stay in the hospital for longer than 5 days, due to AEs or any other reason, the treatment for these cases will be at discretion of the attending physicians. No further blood samples or study procedures will be performed from this point onward. However, the final outcome at discharge will be collected in the case report form (CRF;
*Extended data*
^46^).

At discharge, the participants will be offered a referral to nutrition specialists for a consultation of overweight/obesity management. Patients will also be provided with leaflets on healthy eating and lifestyle behaviours.

While not an RCT, this trial is designed to enroll patients contemporaneously with an observational obesity trial, where patients received standard care, to minimize systematic differences between the intervention (metformin) and control group, i.e. patients have the same inclusion /exclusion criteria, enrolled on same wards, with the same standard of care during the same dengue season (to avoid the issue of viral serotype shifts). 

To minimize selection bias, we have set up a system on the dengue wards, to ensure eligible patients are recruited into both studies in a systematic way. This involves only one study enrolling for a 2-week time block. During that time, if a patient fails screening assessment or declines enrollment into one of the trials, they are not eligible for the other.

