### Treatment and drug dispensation

Metformin will be kept in a dry location below 30°C, in a secure area. A study pharmacist will make up and label individual-participant treatment packs with a trial number. Each pack contains sufficient study drug for 5 days of treatment and will be distributed to study wards as required. All medication storage and administration will be regulated through the central pharmacy to ensure good quality and control of medication handling.

Patients will be recruited into either cohort 1 (low dose) or cohort 2 (high dose). Study drugs will be administered as directly-observed-therapy. Patients will take the first dose of study drug with a light snack as soon as possible after enrolment. The remaining doses will be taken after meals. In case of vomiting within 30 minutes of taking the treatment, one replacement dose will be given. However, if patients continue vomiting after taking the replacement dose, no extra drug will be given thereafter.

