### Data collection

***Clinical evaluation.*** Patients will be reviewed daily until discharge. All clinical symptoms and signs will be recorded in the CRF. An ultrasound scan will be performed on day 5–6 of illness to detect evidence of fluid accumulation. General management decisions will be at the discretion of the attending ward doctors. Details of all AEs and SAEs will be recorded on specific forms, together with an assessment as to whether the events are likely to have been related to any treatment received. All SAEs will be reported promptly to the DMC and ECs according to policy.

***Laboratory evaluation.*** Full blood count (FBC) and POC glucose and lactate tests will be undertaken daily until discharge. An additional POC glucose test will be performed before their evening meal.

In addition, levels of serum albumin, transaminases (ALT/AST), creatinine, total cholesterol, HDL-cholesterol, LDL-cholesterol, triglycerides, and C-reactive protein (CRP) will be measured on alternate days. All tests will be done more frequently when clinically indicated.

Research samples collected daily until discharge will be used for dengue diagnostics (NS1 antigen detection and PCR assays). Residual blood from FBC samples will be collected for daily plasma viraemia levels. Serology tests (Capture IgM/IgG ELISAs) will be performed on enrolment (acute) and discharge/FU (convalescent) samples. Other laboratory investigations will include endothelial, inflammatory and lipid biomarkers (VCAM1, syndecan-1, leptin, adiponectin), using commercially available ELISAs and Luminex kits, immunological tests (T cell phenotype and functional analysis), and immunometabolism (AMPK phosphorylation). RNA will be extracted from a blood sample collected on study day 2, and will be sequenced to investigate gene expression in the metformin treatment group in comparison to the non-treatment group.

At day 28 of illness, final routine (FBC, biochemistry) and research blood samples will be taken to check whether patients have fully recovered from the acute dengue episode.

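### The illness-day 3–8 window can count a pre-dose AST/ALT value as the highest value in patients enrolled on illness day 3, which modestly dilutes the comparison; these endpoints also lack adjustment for the pre-dose value

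*Protocol article*

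**What the plan says.** Under Secondary endpoints, the protocol article lists "platelet nadir and highest AST/ALT between days 3 and 8 of illness". It does not restrict these to samples taken after the first dose or after enrolment. Most of the time-based endpoints beside them, such as fever clearance, time to undetectable viraemia and viraemia area under the curve, are anchored to enrolment or study day.

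Patients qualify if they "are admitted within 72 hours of fever onset" (Inclusion and exclusion criteria). Under Screening, enrolment and retention, those "with clinical suspicion of dengue and less than 72 hours of fever are invited to participate in the trial". At that stage "Blood samples are collected to test for NS1, and AST, ALT and creatinine levels". Dosing comes later: "Patients will take the first dose of study drug with a light snack as soon as possible after enrolment" (Treatment and drug dispensation).

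Under Data collection, "Full blood count (FBC) and POC glucose and lactate tests will be undertaken daily until discharge", whereas the transaminases "will be measured on alternate days", with extra tests when clinically indicated. Patients with "alanine transaminase (ALT) and/or aspartate transaminase (AST) >250 U/L" at baseline are excluded.

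The Statistical analysis paragraph adjusts all comparisons for age, sex and day of illness. It adds the pre-dose value only for the haematocrit increase and the viraemia area under the curve.

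**The concern.** A patient enrolled on illness day 3 has the screening AST and ALT inside the window although no drug has yet been given. For a patient enrolled on day 1 or 2 the same sample lies outside it. The endpoint therefore means slightly different things depending on the day of arrival.

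Where the screening value is the highest in the window, it is the patient's score, and whatever metformin does below that level goes unseen. This pulls the comparison towards no difference. Transaminases are the most exposed because few values are planned. A patient enrolled on day 3 has routine values on about illness days 3, 5 and 7, so one in three is pre-dose.

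The arms are not randomised, so a difference in starting enzyme or platelet levels is possible, and the listed covariates do not include those levels. The Discussion would take improvement in any secondary endpoint, once safety is established, as grounds for a larger randomised trial, so these endpoints should measure what happens after dosing.

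**Working it through.** The article gives no figure for these endpoints to reproduce. Its only power statement concerns the VCAM slope and has no bearing here.

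**Step 1. Who has a pre-dose sample in the window?** Assume the hour of onset H is uniform over 0–24 and the delay from onset to enrolment is uniform over 0–72 hours. H averages 12.

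| Day numbering | Condition for illness day 3 or later | Share |
|---|---|---|
| Onset = day 1, 24-hour blocks | delay ≥ 48 h | 24/72 = 33% |
| Onset = day 1, calendar days | H + delay ≥ 48 | (24 + 12)/72 = 50% |
| Onset = day 0, calendar days | H + delay ≥ 72 | 12/72 = 17% |
| Onset = day 0, completed 24-hour blocks | delay ≥ 72 h | 0% |

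The overlap exists under three of the four conventions.

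**Step 2. What does the pre-dose value do?** Let B be the pre-dose value and M the highest post-dose value. For these patients the score is max(B, M). Suppose M would be M0 untreated and M1 treated, with M1 < M0.

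- Both above B: the full effect M0 − M1 is counted.
- M0 above B and M1 below it: only M0 − B is counted.
- Both below B: nothing is counted.

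As an invented illustration, pre-dose AST 210 U/L followed by 150 and 90 scores 210. For a nadir the pre-dose value is a ceiling in the same way. Platelets are counted daily and usually fall after enrolment, so it seldom binds.

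**Step 3. How large is the dilution?** All inputs here are assumptions: 60 v 60; baseline log ALT normal with mean ln 60 and SD 0.7; mean log rise after enrolment 0.3 or 1.0 (SD 0.5–0.6); two post-dose samples at 60% and 100% of the patient's change; noise SD 0.1; true effect −0.3 log units at the last sample; linear regression including baseline. With 33% enrolled inside the window:

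| Mean rise | Effect, current window | Effect, post-dose only | Shrinkage | Power loss |
|---|---|---|---|---|
| 0.3 | −0.229 | −0.253 | 1 − 0.229/0.253 = 9.5% | about 3 points |
| 1.0 | −0.287 | −0.290 | 1 − 0.287/0.290 = 1.0% | about 0 |

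Shrinkage is proportional to the share q enrolled inside the window:

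- q = 17%: 9.5% × 17/33 = 4.9% at rise 0.3, and 1.0% × 17/33 = 0.5% at rise 1.0.
- q = 50%: 9.5% × 50/33 = 14% at rise 0.3, and 1.0% × 50/33 = 1.5% at rise 1.0.

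Simulating directly at 17% and 50% agreed closely. The largest power loss was about 4 points.

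A cruder bound gives affected patients no effect at all and leaves the SD unchanged. The effect is then multiplied by 1 − qp, where p is the share of those enrolled in the window whose extreme is the pre-dose value. With q = 0.50 and p = 0.30 the factor is 0.85, and a comparison with 80% power falls to 66%. This overstates the loss, because the floor also narrows the spread of scores.

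**Step 4. Does the window create baseline imbalance?** If one arm starts δ higher in log ALT and all else is equal, B and every post-dose value rise by δ. Then max(B, M) and M both rise by δ. With δ = 0.3, no treatment effect, rise 0.3 and no baseline covariate, the estimated arm difference was 0.298 with the current window and 0.298 with post-dose values only (33% enrolled inside the window). Changing the samples alone does not remove it. A pre-dose covariate does.

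**The case against.** The strongest reply is that an illness-day window applied alike to both arms is a natural choice in a disease described by illness day, and that whether an enrolment sample counts is a derivation rule for the analysis plan. The article places the critical phase at about days 4–6, so most extremes should follow the first dose. Baseline transaminases are capped at 250 U/L, and clinically indicated tests add post-dose values. The study is exploratory and is not sized on these endpoints.

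Much of this stands, and it places the effect towards the small end. The cap limits how high the floor can be, but not how often it is the highest value. Adjustment for day of illness removes an average difference between early and late enrolees, but not the floor. The reply about the analysis plan is weaker: the article itself fixes both the window and the list of endpoints that receive pre-dose adjustment, so this is a stated rule and not an omitted detail.

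A reader might infer three stronger points that the documents do not support:

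- *The effect is zero by construction in affected patients.* The pre-dose value is only a floor, so prevention of a rise above it still counts (step 2).
- *The window lets baseline differences into the comparison.* They enter equally with post-dose values alone (step 4). The cause is the missing covariate.
- *Platelet nadir is affected as much as the enzymes.* Daily counts and the usual fall after enrolment make that unlikely, and the calculation covers ALT only.

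**Conclusion.** The point holds as a minor defect of definition, mainly for highest AST/ALT. Under three of four ways of numbering illness days, some patients have a pre-dose value inside the window and others do not, and nothing in the article removes it or adjusts for it.

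The consequence is dilution towards no difference: roughly 1% to the low teens of per cent of the effect, with a power loss of 0 to a few points. That range rests on uniform arrival (17–50% enrolled inside the window) and on an assumed enzyme rise and treatment effect. The documents supply none of these. If onset is day 0 and only completed 24-hour blocks count, the overlap disappears.

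The absence of pre-dose adjustment for these endpoints is a separate weakness. Its size depends on a baseline difference between the arms that cannot be known in advance. The primary safety endpoint is not affected.

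**What to change.** Make three changes, all before analysis:

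1. Define illness day 1, stating whether days are calendar days or 24-hour blocks.
2. Derive platelet nadir and highest AST/ALT from samples taken after the first dose (in controls, after the enrolment sample) and within illness days 3–8. Keep the day-3 start, since dropping it would give early enrolees a longer window.
3. Add the pre-dose platelet count or AST/ALT value as a covariate, as the article already does for haematocrit and viraemia.

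No new data are needed: screening transaminases are collected, and the planned pre-dose haematocrit adjustment implies a pre-dose blood count. The cost is a few sentences and some missing outcomes, because a patient with no post-dose sample in the window has no value to score. That is most likely for transaminases in patients discharged early, and the number should be reported by arm.

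### Viraemia clearance, and fever clearance if dated to the start of the 48-hour period, run from enrolment in all patients, so those already clear before the first dose count as immediate events and dilute any true effect

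*Protocol article*

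**What the plan says.** The Secondary endpoints section of the protocol article times virological clearance as "time from enrolment to first undetectable viraemia and first negative NS1 measurement". It defines fever clearance as "the time from enrolment to sustained body temperature <37.5°C for 48 hours". Neither definition sets a condition on the patient's state at enrolment.

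Under Inclusion and exclusion criteria, the two relevant entry conditions are that patients "are NS1 rapid antigen test positive" and "are admitted within 72 hours of fever onset". Screening, enrolment and retention lists the screening tests, and viral PCR is not among them. Treatment and drug dispensation places the first dose after enrolment.

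Statistical considerations gives the population: "The primary analysis population will include all patients from cohort 1 and cohort 2, plus 60 controls as mentioned previously". The model is "Cox regression for time-to-event endpoints (fever clearance time, time to first undetectable viremia measurement, time to first negative NS1 measurement"). Every comparison is adjusted for age, sex and day of illness. The pre-dose value is added only for the haematocrit increase and the viraemia area under the curve, not for the clearance times.

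**The concern.** A time-to-clearance analysis should follow patients who still have something to clear. A positive NS1 test shows antigen, not detectable viraemia. Fever onset within 72 hours is history, not a current temperature. A patient already clear at enrolment therefore meets the event definition at once, before any study drug, and carries no information on metformin.

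Two consequences need to be kept apart. If the share already clear is the same in both arms, these events pull the hazard ratio towards 1 and cost power. If it differs for reasons the covariates do not capture, they create an apparent effect. The arms are not randomised, and only one of the two studies enrols in each two-week block.

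Reduced viral replication is a stated hypothesis. The Discussion also says that, with safety established, improvement in any secondary endpoint would justify a larger randomised trial, so a distorted clearance result could influence that decision.

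**Working it through.** **No figure to reproduce.** The only power statement concerns the VCAM slope. The article gives no event rate or power for the clearance endpoints, and no share of patients already clear at enrolment.

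**What follows from the text.** The origin is enrolment, the event is the first undetectable result, the population is all patients, and the first dose comes later. An undetectable enrolment sample therefore gives a clearance time of 0. For fever this depends on dating. If the event is placed at the start of the 48 afebrile hours, a patient afebrile from enrolment also has time 0. If it is placed at the end, the earliest possible event is at 48 hours, after the first dose. For NS1, an event at enrolment could arise only if the research assay disagreed with the positive rapid test.

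**Assumed inputs.** 60 per arm (from the article), daily sampling (from the article), 5 days of follow-up, control median clearance 3 days, exponential times, true hazard ratio 1.75 in patients still at risk, and a share f already clear in both arms.

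**Dilution by hand.** The probability of clearing by day 5 is 1 − 2^(−5/3) = 0.685 in controls and 1 − 2^(−5×1.75/3) = 0.868 under treatment, mean 0.776. Time-zero events are d0 = 120f and later events are d = 120(1 − f) × 0.776. With equal shares the time-zero events point to a log hazard ratio of 0, so approximately

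log HR(all) = log(1.75) × d/(d + d0), with log(1.75) = 0.560.

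For f = 10%: d0 = 12, d = 83.8, weight 0.875, log HR 0.490, HR 1.63. For f = 20%: d0 = 24, d = 74.5, weight 0.756, log HR 0.423, HR 1.53.

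**Dilution by simulation** (Cox model, Efron ties, times rounded up to whole days, 600 runs per row, no covariates):

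| Already clear, both arms | HR by hand, all | HR simulated, all | HR simulated, at risk only | Power, all | Power, at risk only |
|---|---|---|---|---|---|
| 5% | 1.69 | 1.69 | 1.76 | 72% | 74% |
| 10% | 1.63 | 1.64 | 1.75 | 70% | 75% |
| 20% | 1.53 | 1.55 | 1.78 | 55% | 67% |
| 30% | 1.43 | 1.42 | 1.75 | 42% | 59% |

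A separate simulation with the planned adjustment for day of illness gave 1.71, 1.60 and 1.58 with about 6%, 16% and 23% already clear in both arms, against about 1.76 to 1.80 after restriction. The dilution survives the planned adjustment.

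**Unequal shares, no drug effect, no covariates.** With 15% v 5% already clear there are 9 v 3 time-zero events. The score is 9 − 6 = 3. The information is 12/4 = 3 at time zero plus about 74/4 = 18.5 from the later events (108 × 0.685 = 74). So log HR is about 3/21.5 = 0.14 and HR 1.15. The simulation gave 1.15 with 9% rejection, against 1.00 and 5% in patients at risk. At 30% v 10% it gave 1.37 with 29% rejection, against 1.00 and 6%.

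**Unequal shares arising through day of illness, no drug effect.** With 11% v 5% already clear (500 runs), the all-patient hazard ratio was 1.49 unadjusted and 0.99 adjusted for day of illness (6.4% rejection). Restricted and adjusted, it was also 0.99 (6.2%). The separate adjusted simulation agreed: 1.03 for all patients, 1.02 restricted.

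**The case against.** A reader might infer that the planned comparison is biased and prone to false positives. The documents do not support that. Day of illness, an obvious driver of being already clear, is in every model, and when the imbalance arises through it, the planned adjustment removes the bias. The hazard ratios of 1.15 to 1.37 apply only to an imbalance beyond age, sex and day of illness. They also assume that patients still at risk are otherwise exchangeable, so the return to 1.00 after restriction is built in.

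The endpoint sentence also names NS1, and a reader might extend the point to it. The positive entry test largely rules that out.

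For fever, the 48-hour wording allows either dating. A simple exclusion of everyone below 37.5°C at enrolment would lose patients with a transiently low reading whose fever returns, and whose clearance is genuinely after dosing. It would also sit awkwardly with the stated intention-to-treat analysis. This stands, and it shapes the fix.

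The share already clear may be small in NS1-positive patients early in illness. At 5% the loss is slight (1.69 against 1.75, power 72% against 74%). This stands as a limit on importance.

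Finally, no sentence says that clear patients count as time-zero events, and an unseen analysis plan could add an at-risk rule. But the article does fix the origin, event, population, model and covariates, and applied together they produce that result.

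**Conclusion.** The point holds for viraemia clearance, and for fever clearance if the event is dated to the start of the 48 hours. As written, patients already clear before dosing enter the Cox model as immediate events.

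The established consequence is dilution: a true hazard ratio of 1.75 becomes about 1.7 with 5–6% already clear in both arms and about 1.6 with 16–23%. Bias in either direction is conditional on an imbalance that age, sex and day of illness do not explain, and the documents give no evidence of one.

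The sizes rest on assumed clearance times, follow-up and shares already clear. These are secondary endpoints in an exploratory study focused on safety, so the matter is modest. It is still worth correcting, because restriction on pre-treatment data introduces no post-treatment selection and, in these simulations, gains power despite the smaller sample.

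**What to change.** **Viraemia.** Define time to first undetectable viraemia among patients with detectable viraemia in the enrolment (pre-dose) sample, and count only later samples. Apply the same rule in controls, using their enrolment sample.

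**Fever.** State that the event is dated to the start of the 48-hour afebrile period. Make the main comparison among patients at 37.5°C or above at enrolment, and keep the all-patient analysis as a sensitivity analysis so that patients with a transiently low reading are not lost.

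**Both.** Keep the planned adjustment for age, sex and day of illness, and report the number already clear at enrolment by arm. NS1 clearance needs no change on this account.

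**Cost.** A sentence or two in the endpoint definitions, and a slightly smaller sample for these secondary endpoints. Daily viraemia sampling is already planned, so no extra blood sampling is needed.
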